## Methods

### Study design and plan

The study is a phase IV, multi-site, 2-arm, 52-week, randomised, double-blind, placebo-controlled trial of 2 g of NAC per day (taken as two 500 mg capsules twice per day or matching placebo), in 168 participants diagnosed with SZ (see Fig. 1 for study outline). In addition to baseline assessments, follow-ups will take place at 8, 24 and 52 weeks (see Table 1 for a list of study assessments). A subsample at the Melbourne site will be invited to undergo a brain scan using MRI (*N* = 42). Scans will be performed at baseline, 8 and 52 weeks. The study protocol was approved by the St Vincent’s Hospital Human Research Ethics Committee (HREC-A HREC-D 030/16), this committee has jurisdiction over all the participating sites. An executive steering committee (all authors) oversees project planning, conduct and ongoing data collation.

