### Participants

Forty-two patients will be recruited from each of the sites, with a total target of 168 participants aged 18–65 years meeting DSM-5 criteria for SZ. Investigators at each site will be responsible for recruiting participants through advertising and engagement with clozapine clinics associated with their site. As we are interested in clozapine patients who have residual symptoms, all potential participants will be screened and assessed for eligibility. The following inclusion criteria are to be adhered to: (1) Aged 18–65 years; (2) Confirmed diagnosis of SZ via clinical interview; (3) Have been on clozapine at an adequate dose for at least 6 months, ascertained by a current serum level of >350 mcg/L and with residual symptoms (see 4.)^1^; (4) Have a PANSS score of ≥60 or at least two negative symptom items of >4^2^; (5) Have the capacity to provide consent to the study; and (6) Be utilising effective contraception (i.e., oral or barrier contraception) if female and of childbearing age. In addition, the following exclusion criteria will be applied: (1) Participants who are currently taking NAC; (2) Participants who are allergic to NAC or any component of the preparation; (3) Participants who are currently prescribed nitro-glycerine (significant potential interaction with NAC); (4) Participants who have diabetes mellitus and on insulin replacement (including exenatide) (moderate interaction); (5) Participants taking Aralen (moderate interaction); (6) Participants who regularly take >200 mg/day selenium (moderate interaction); (7) Participants who regularly take anticoagulants (moderate interaction) (excluding aspirin and non-steroidal anti-inflammatories); (8) Change in medication from clozapine to another antipsychotic; (9) Participants with known primary or secondary autoimmune disorders; (10) Recent gastrointestinal ulcers; (11) Recent renal stones; and (12) Females who are pregnant or lactating.

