Power was calculated to detect a medium effect size of *d* = 0.5 as described in an earlier NAC and SZ paper [5] and the calculations followed the method described by Diggle et al. [23]. These calculations assumed one primary outcome measure (PANSS Negative scores), four assessment points (baseline, 8-weeks, 24-weeks, and 52-weeks follow-ups), a study-wide Type I error rate (α) of 0.01, a Type II error rate (β) of 0.10 (power of 0.90), a correlation of post-treatment scores with baseline measurements (ρ) of 0.70, employing a two-tailed statistical test. To detect the effect size of *d* = 0.5, 45 participants in each of the control and intervention groups will be required. Allowing for up to 46 % attrition (based on a 20 % dropout over the first 8 weeks and a further 30 % dropout over the ensuing 44 weeks), a total of 168 participants, or 84 in each group will be recruited. Similar attrition rates are reported in other treatment trials with treatment resistant SZ. To accommodate the required number of patients, at least 42 will need to be recruited from each of the four study sites. For the MRS component, groups of 15–20 are widely accepted as an appropriate size to permit appropriate neuroimaging analysis. As noted earlier the anticipated numbers, including drop out and ineligibility for the MRS component are 40 at baseline, 36 at 8-weeks and 52-weeks. Thus, the current study will be adequately powered for the MRS component.

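### The anticipated MRS numbers (40, 36, 36) do not follow the trial's own dropout rates, and the claim of adequate MRS power is unsupported

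*Protocol article*

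**What the plan says.** All the relevant figures are in the Protocol article, mostly in the sample-size paragraph of the Participants section.

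- **Trial-wide dropout.** The recruitment target is inflated as follows: "Allowing for up to 46 % attrition", which is "based on a 20 % dropout over the first 8 weeks" and "a further 30 % dropout over the ensuing 44 weeks". The paragraph adds that comparable rates are seen in other trials in treatment-resistant schizophrenia.
- **MRS numbers.** A few sentences later, "the anticipated numbers, including drop out and ineligibility for the MRS component are 40 at baseline, 36 at 8-weeks and 52-weeks".
- **MRS criterion and conclusion.** The size is justified by the statement that "groups of 15–20 are widely accepted as an appropriate size to permit appropriate neuroimaging analysis", from which it concludes: "Thus, the current study will be adequately powered for the MRS component".
- **Who is scanned.** Under Study design and plan, "A subsample at the Melbourne site will be invited to undergo a brain scan using MRI" (N = 42), with scans at baseline, week 8 and week 52. On site targets, "Forty-two patients will be recruited from each of the sites".
- **After withdrawal.** Under Withdrawal criteria, the follow-up to be attempted for a withdrawn participant is a review of medications and adverse events. No scan is listed.

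**The concern.** The MRS participants are ordinary trial participants from one site. They take the same capsules for the same 52 weeks and face the same reasons to leave, plus the burden of a scanner visit. Yet the article expects half the trial's planned loss among them by week 8, and no loss at all over the period in which the trial plans to lose a further 30%. The MRS figures are said to include dropout already, so the gap cannot be put down to dropout being handled elsewhere.

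Week 52 matters to the MRS aims. The Biological mechanisms section assigns it to long-term change, the Research aims predict an increase in cortical glutathione, and the Statistical analyses section lists cortical glutathione as a process outcome to be modelled. If the week 52 comparison rests on far fewer scans than stated, a null result could be read as evidence against the proposed mechanism because the article has promised adequate power.

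**Working it through.** **Inputs.** From the Participants section: 40 MRS participants at baseline and 36 at weeks 8 and 52; 20% dropout to week 8 and a further 30% to week 52; up to 46% overall; 15–20 per group as the criterion; 45 completers per arm needed for the primary outcome. From Randomisation and blinding: 1:1 allocation.

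**Step 1: does the article's own dropout arithmetic work for the main trial?** Recruitment per arm = completers ÷ (1 − dropout) = 45 ÷ 0.54 = 83.3, rounded up to 84, or 168 in total. This matches the article, so 46% is the rate used to set the sample size. (20% followed by 30% of those remaining gives 1 − 0.80 × 0.70 = 44%; simple addition gives 50%. All three are carried below.)

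**Step 2: what loss do the MRS figures imply?** Week 8: 1 − 36/40 = 10%. Weeks 8 to 52: 1 − 36/36 = 0%.

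**Step 3: apply the trial's rates to 40 baseline scans.**

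| Time | Dropout | Scans | Per arm | Stated |
|---|---|---|---|---|
| Week 8 | 20% | 40 × 0.80 = 32 | 16 | 36 (18 per arm) |
| Week 52 | 44% | 40 × 0.56 = 22.4 | 11.2 | 36 (18 per arm) |
| Week 52 | 46% | 40 × 0.54 = 21.6 | 10.8 | 36 (18 per arm) |
| Week 52 | 50% | 40 × 0.50 = 20 | 10 | 36 (18 per arm) |

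Starting from all 42 invited does not change the picture: 42 × 0.80 = 33.6 at week 8 (16.8 per arm) and 42 × 0.54 = 22.7 at week 52 (11.3 per arm). No combination gives 36 at either time.

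**Step 4: compare with the criterion.** Week 8, at 16 per arm, is within 15–20. Week 52, at about 11, is below it. Keeping 15 per arm (30 in total) from 40 allows 1 − 30/40 = 25% total loss. After 20% by week 8, that leaves 1 − 30/32 = 6% for the rest of the year, against the planned 30%. At 46% dropout, 30 ÷ 0.54 = 55.6, so 56 baseline scans would be needed.

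**Step 5: what could these numbers detect?** This is illustration only, since the article gives no MRS effect size, alpha or power. I assume a two-sided alpha of 0.05 and 80% power in a two-sample comparison (noncentral t). For baseline adjustment I multiply by √(1 − ρ²), borrowing ρ = 0.70 from the PANSS negative calculation: √0.51 = 0.714.

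| Per arm | Detectable d, unadjusted | Detectable d, adjusted |
|---|---|---|
| 18 (as stated) | 0.96 | 0.96 × 0.714 = 0.69 |
| 11 (trial's dropout) | 1.26 | 1.26 × 0.714 = 0.90 |

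**The case against.** **A ceiling is not a forecast.** The 46% is worded as an upper allowance, whereas the MRS figures are anticipated numbers, and the two may legitimately differ. This stands in part: about 11 per arm is what the planning rates give, not a prediction. But the article offers no lower rate for the subset, and zero loss after week 8 cannot be squared with a further 30%. Week 52 misses the criterion once total loss exceeds 25%.

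**The power claim is simply false.** A reader might infer this, but the documents do not support it across the board. Week 8 meets the stated convention even at the trial's dropout. With no MRS effect size given, power cannot be computed, so unsupported is the accurate word.

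**Power for d = 0.5.** It is tempting to quote low power at that effect. It is the PANSS negative effect, not a glutathione effect, and the trial's alpha is 0.01 rather than 0.05. The Statistical analyses section also plans baseline adjustment and a likelihood model using all visits, so those lost after week 8 still contribute. A completers-only, unadjusted figure would show only the unfavourable end. Hence both columns in the working, marked as illustration. The model does not restore the missing week 52 scans.

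**Two side points do not carry weight.** Scanning 40 of Melbourne's 42 would need about 95% of the site (40/42), but the sample-size text words 42 as a minimum, so this is a feasibility doubt and not an error. The MRS figures are introduced as having been given before, and the text shown earlier gives only N = 42; Fig. 1 is not shown and could contain them, so this cannot be called a mistake.

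**Conclusion.** The concern holds in a bounded form. The stated 36 at weeks 8 and 52 is not reconciled with the dropout that sets the trial's sample size. On those rates, expected scans are about 32 at week 8 (16 per arm) and about 22 at week 52 (about 11 per arm; 10 to 11.2 for dropout of 50% to 44%). The claim of adequate MRS power is unsupported at all time points, because it rests on a group-size convention, and at week 52 it fails that convention too.

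This rests on three assumptions: 40 scanned at baseline, even loss across arms, and MRS participants dropping out at the trial-wide planning rate for want of any other stated rate.

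Severity is moderate. MRS is a process outcome in a one-site subset, and nothing here touches the primary sample size, the randomisation or the primary analysis.

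**What to change.** 1. Restate the expected scans at baseline, week 8 and week 52 as about 40, 32 and 22, or give the basis for a separate, lower dropout rate in the MRS subset.
2. Replace the adequate-power sentence with a statement of expected precision or detectable effect at those numbers, naming the alpha, the power and any baseline correlation assumed for glutathione.
3. Describe the week 52 MRS comparison as exploratory and report it as estimates with confidence intervals. Both scan times can keep the purposes the article gives them; promoting week 8 to the main MRS contrast would be a design preference that this error does not require.

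The cost is wording only. No visit, scan or participant is added. The one downside is that the article's claim for the MRS component becomes less favourable.

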### Consent

The process of consent will be in accordance with the Declaration of Helsinki. All eligible patients will be fully informed that they are being asked to participate in a RCT. The procedures involved in the study, and the chances of being assigned randomly to one of two groups will be explained verbally and via an information sheet approved by the hospital’s Human Research Ethics Committee. All participants will provide informed consent by reading the information sheet, asking any questions they need to and subsequently signing the consent form in front of an independent witness. Participants will be made aware of their right to withdraw from the study at any time without any effects on their clinical management.

### Randomisation and blinding

The study procedure will follow the SPIRIT guideline [24]. The trial is a randomised, controlled, double-blinded superiority trial of two parallel patient groups. Randomisation will be performed independently of the researchers by an independent researcher and will employ block randomisation (2 × 4) with a 1:1 allocation to NAC or placebo. Allocation will be concealed from local investigators, who will assign a number to the participant that will be linked to a prescription from the associated pharmacy. All participants will be dispensed the same number of capsules each month.

### Withdrawal criteria

Participants may be withdrawn from the study for the following reasons: cessation of clozapine; non-adherence to medication; emergence of adverse events; pregnancy/cessation effective contraception; or withdrawal of consent. If a participant is prematurely withdrawn from the study for any reason after product administration, the investigator will make every effort to perform these follow up assessments: review of medications and adverse events. This information will be recorded in the case report form (CRF). In all cases, the reason for withdrawal will be recorded in the CRF.

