### Treatment of participants

The trial treatments are NAC and placebo. Participants must take 2 capsules twice per day (total 2 g of NAC) or matched placebo for 52 weeks. NAC is a GSH precursor. It is very efficiently bioavailable and is rapidly deacetylated by the liver into cysteine. Plasma cysteine levels can be rapidly increased by NAC supplementation. NAC rapidly and safely increases plasma cysteine levels, indirectly replenishing depleted systemic GSH. It is available over the counter and is approved in Australia by the Therapeutic Goods Administration (TGA) in injectable and inhalant forms for treatment of paracetamol overdose.

The NAC and placebo capsules will be identical in colour, size and shape, and will be packaged in identical bottles. NAC has a mild odour and to cover this difference between placebo and NAC, a sachet of NAC powder will be placed in all medication bottles so the same smell is present for all study capsules. Each of the treatments will be clearly labelled with a treatment number by an independent researcher. The trial products will be stored in accordance with manufacturer’s instructions which adopt Pharmaceutical Good Manufacturing Practice. Until dispensed to the participants, the trial products will be stored in a securely locked area, accessible only to authorised personnel, in accordance with GCP drug storage requirements.

Participants will be required to take the capsules as instructed during the 52 weeks of the study. At each assessment session they will be asked to return all unused capsules which will be counted for compliance rate. If less than 50 % of the capsules have been taken at any assessment point this will be viewed as non-compliance.

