### Statistical analyses

Data will be analysed using R 3.1.2 (R Foundation for Statistical Computing, Vienna, Austria and SPSS where relevant). Intention-to-treat analyses will be employed to prevent over-estimation of efficacy. Categorical variables will be analysed using chi-squared tests (or Fisher’s exact test for small samples). A mixed-effects model, repeated measures (MMRM) approach will be used to examine the longitudinal profile of all continuous variables at weeks 8, 24, and 52 post-baseline. For all MMRM analyses, baseline scores will be used as covariates and the models will include pre-specified fixed effects of treatment, site, and time, and treatment-by-time and treatment-by-site interactions.

The MMRM modelling for the primary outcome measure – PANSS negative scores and CAINS scores – will also include baseline PANSS Positive, Negative, and General Psychopathology scores, as covariates. The secondary outcomes consist of MANSA, AQoL and MCCB global score, while the process outcomes include GSH concentrations peripherally and cortically, respectively.

Secondary analyses using Analysis of Covariance will be conducted to compare change scores during treatment and follow-up phases for all primary, secondary, and process outcomes using treatment group as a main effect with the baseline score as a covariate. Site will not be included in the analysis for the MRS data, but will be for the peripheral data. Correlational analyses will also be performed to examine for relationships between outcome variables (i.e., treatment response with cognition and GSH levels, peripherally and cortically).

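### No PANSS or CAINS rating is planned after withdrawal, so the intention-to-treat claim rests entirely on an untestable missing-at-random assumption

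*Protocol article*

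**What the plan says.** The Withdrawal criteria section of the protocol article gives these grounds on which a participant may be withdrawn from the study: "cessation of clozapine; non-adherence to medication; emergence of adverse events; pregnancy/cessation effective contraception; or withdrawal of consent". Only the last is a decision to end participation; the first three concern treatment. Once someone is withdrawn on any ground after dosing has begun, "the investigator will make every effort to perform these follow up assessments: review of medications and adverse events". The primary outcome instruments are not on that list.

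Treatment of participants adds a capsule-count rule: "If less than 50 % of the capsules have been taken at any assessment point this will be viewed as non-compliance".

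Statistical analyses states: "Intention-to-treat analyses will be employed to prevent over-estimation of efficacy". For the model: "A mixed-effects model, repeated measures (MMRM) approach will be used to examine the longitudinal profile of all continuous variables at weeks 8, 24, and 52", with the baseline score as a covariate. The closing paragraph of that section handles attrition by likelihood methods, multiple imputation or latent growth models, all under a missing-at-random assumption.

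The power paragraph under Participants allows for up to 46% attrition, built from 20% in the first 8 weeks and 30% in the following 44. PANSS and CAINS are scheduled at baseline and weeks 8, 24 and 52 (Primary outcome measures, Table 1).

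**The concern.** An intention-to-treat effect is the difference between everyone randomised to NAC and everyone randomised to placebo, whether or not they kept taking the capsules. Estimating it needs outcomes from people who have stopped treatment. The withdrawal text merges stopping treatment with leaving the study, then names what will be sought afterwards and leaves efficacy out.

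Every PANSS value that reaches the model from a withdrawn participant therefore dates from before withdrawal. A missing-at-random model fills the gap by projecting that person's course from similar participants in the same arm who stayed. If people leave because of adverse events, poor adherence or stopping clozapine, that projection may be too favourable to NAC. This is the inflation that the intention-to-treat statement is meant to guard against. Without ratings after withdrawal, the trial cannot check the assumption, and no later analysis plan can recover interviews that were never held.

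**Working it through.** **Inputs from the article:** 168 randomised, 84 per arm; 45 per arm needed before attrition; attrition up to 46%, from 20% by week 8 and a further 30% by week 52; design effect d = 0.5; correlation 0.70; two-sided α = 0.01.

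**1. The plan's own figure.** n = 45 / (1 − 0.46) = 83.3, rounded up to 84 per arm and 168 in total. This reproduces. The inflation treats leavers as contributing nothing, which fits a plan that seeks no outcome from them.

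**2. Attrition by week 52.** If the 30% applies to those still present at week 8, the total is 1 − 0.80 × 0.70 = 0.44. The article states 46%. Both are carried forward; the gap is small and on the cautious side.

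**3. Who lacks which rating.**
- Baseline: PANSS is an entry criterion, so all 168 have it.
- Any rating after baseline: 0.20 × 168 = 33.6, so about 34 leave before the first one at week 8. About 134 (80%) have a week 8 value.
- Week 52: 0.44 × 168 = 73.9 and 0.46 × 168 = 77.3, so 74 to 77 lack it.
- Left between weeks 8 and 52: 74 − 34 = 40, up to 77 − 34 = 43. These give week 8 and perhaps week 24 values, which the model uses.

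**4. Can the model be fitted?** Yes. Assume 84 per arm, correlation 0.70 between all visits, d = 0.5 at every visit, 20% with no rating after baseline and 46% gone by week 52. Split the later losses in any way between weeks 8–24 and 24–52. After baseline adjustment the residual covariance of the three visits is (1 − 0.70)I + (0.70 − 0.49)J, where I is the identity matrix and J a matrix of ones. Summing the information over the dropout patterns gives a standard error of 0.144 to 0.146 for the week 52 effect. Power is then Φ(0.5/0.144 − 2.576) = 0.815, falling to 0.804 at the other end of the range. For the average over visits it is about 0.99. These figures hold only if data are missing at random.

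**5. What missing at random could hide.** Assume the worst case: every NAC leaver loses all benefit, whatever the reason. Assume also equal attrition in both arms and an on-treatment effect of 0.50 at every visit. The effect in all randomised is 0.50 × (1 − proportion gone):

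| Visit | Gone | Effect in all randomised | Missing-at-random model |
|---|---|---|---|
| Week 8 | 20% | 0.50 × 0.80 = 0.40 | about 0.50 |
| Week 52 | 44% | 0.50 × 0.56 = 0.28 | about 0.50 |
| Week 52 | 46% | 0.50 × 0.54 = 0.27 | about 0.50 |

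The last column stays near 0.50 because every rating the model sees was taken before withdrawal.

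**The case against.** There is a fair case that the plan is less exposed than this suggests.

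- The withdrawal wording is permissive (may be withdrawn), and a capsule count below half is called non-compliance without any statement that the person is then removed. This stands: a reader might infer an automatic removal rule, and the text does not contain one.
- The 46% is an all-cause allowance with no breakdown. Some of these people will refuse further contact or be lost, and no follow-up rule would bring them back. This stands: the article does not support the inference that the plan itself creates all of the missing data.
- A reader might conclude that 46% of participants yield no PANSS at all, or that an intention-to-treat analysis is impossible. Neither follows. Everyone has a baseline score, about 80% reach week 8, and the model can be fitted by randomised group.
- Multiple imputation, also named in the plan, can keep the roughly 34 participants who have only a baseline score. It can, but under the same assumption, so it adds no evidence about outcomes after withdrawal.
- The article condenses a fuller protocol, and sensitivity analyses often sit in the analysis plan. That would answer a complaint about silence. Here the text states which assessments will be sought, and efficacy is not among them. Sensitivity analyses can explore the gap but cannot fill it.

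**Conclusion.** The point holds in a limited form. The Withdrawal criteria text does not fit the aim declared under Statistical analyses: treatment-related withdrawal ends efficacy follow-up, while the analysis is meant to describe everyone randomised. On the plan's rates, about 34 of 168 (20%) would have no PANSS after baseline and 74 to 77 (44–46%) none at week 52. How many of these could have been rated is unknown, so the counts are ceilings. What is weakened is the standing of the estimate as an intention-to-treat effect, not the ability to compute one.

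The 0.27–0.28 at week 52 and 0.40 at week 8 are worst-case illustrations that rest on total loss of benefit in every leaver. It is tempting to read 0.27 as the expected true effect, but the article gives nothing on outcomes after stopping, so it cannot support that. The true dilution may lie anywhere from none up to that bound. The change is worth making because it is cheap and cannot be made retrospectively.

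**What to change.** Reconcile Withdrawal criteria with Statistical analyses by treating stopping study treatment and leaving the study as separate events. Participants who stop treatment but still consent remain in the already scheduled week 8, 24 and 52 PANSS and CAINS assessments, and those ratings enter the primary analysis by randomised group. Record separately who withdrew consent or was lost, so that the unavoidable share becomes known. Nothing about who stops treatment, or when, needs to change. An additional rating at the time of stopping is optional, since it would be an unscheduled visit.

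The cost is an amendment to the protocol and consent wording, more interviews and some refusals. The ceiling across four sites is 34 / 4 = 8.5 extra interviews per site at week 8 and 77 / 4 = 19.25 at week 52; the number at week 24 lies between these. All fall within the visit load already planned for 42 participants per site. According to Trial status, recruitment had not begun when the article was submitted, so on that timing the amendment could apply from the first participant.
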